### Randomization and blindness

An independent statistician, who will not participate in the study or data management, will generate a randomization list using an online tool^2^ with an allocation ratio of 1:1 and block sizes of 2 and 4. Randomization will be performed intraoperatively at the time of surgical specimen removal to minimize post-randomization exclusions. The generated random sequences will be securely sealed in sequentially numbered opaque envelopes stored in a locked cabinet. An independent researcher, who is responsible for patient enrollment, will immediately open the envelope following the removal of surgical specimen to obtain the randomization assignment. All patients will receive either an ESPB or ICNB based on randomization at the end of the surgery under anesthesia, ensuring that patients are blinded to their group allocations. Additionally, investigators involved in the postoperative outcomes data collection and follow-up assessments will remain masked to group allocation. Group allocation will remain concealed until the trial is closed to accrual and the final patient has completed the 3-month study period following surgery.

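### The researcher who enrols patients also opens the randomization envelopes, so with blocks of 2 and 4 the next allocation can be guessed correctly up to 72% of the time

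*Protocol article*

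**What the plan says.** All of the following is in the protocol article, Randomization and blindness, unless stated otherwise.

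- List: "An independent statistician, who will not participate in the study or data management, will generate a randomization list", with an "allocation ratio of 1:1 and block sizes of 2 and 4". No stratification factor is named and the trial has one center, so this reads as one list.
- Concealment: the sequence is "securely sealed in sequentially numbered opaque envelopes stored in a locked cabinet".
- Timing: "Randomization will be performed intraoperatively at the time of surgical specimen removal to minimize post-randomization exclusions". Table 1 places eligibility screening and consent earlier, at the preoperative visit.
- Who opens the envelope: "An independent researcher, who is responsible for patient enrollment, will immediately open the envelope following the removal of surgical specimen".
- Masking: patients are blinded, and "investigators involved in the postoperative outcomes data collection and follow-up assessments will remain masked to group allocation". The enrolling researcher is not among those said to be masked.
- General statement: "Group allocation will remain concealed until the trial is closed to accrual" and follow-up of the last patient is complete.

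**The concern.** Concealment requires that whoever decides which patients enter the trial cannot foresee the next arm. Opaque envelopes protect the contents of future envelopes. They give no protection against someone who has opened all the earlier ones and can reason from small, balanced blocks. Here that person is the enroller. The general statement that allocation stays concealed cannot be true of the person who opens the envelopes.

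There are two points at which foresight could be used. The first is the preoperative visit, where patients are screened and consent. The second is the step from consent to randomization. Placing randomization at specimen removal implies that some consented patients may never reach it. At that step the next envelope belongs to the patient on the table, so no queue dilutes the guess.

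If entry were influenced by the expected arm, the groups could differ before treatment. The planned regression adjusts for age, sex, type of surgery and number of ports (Statistical analysis), and selection on anything else would remain. The primary outcome is self-reported resting pain, and the protocol states an expectation that ESPB will do better. Both make comparable groups important.

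**Working it through.** The plan states no figure for predictability, so there is none to reproduce.

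**Inputs from the article.** 1:1 allocation, blocks of 2 and 4, one list, and an enroller who sees each past allocation.

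**Assumptions.** Blocks of 2 and 4 are equally frequent, so the average pair of blocks covers 2 + 4 = 6 patients. The enroller knows both sizes and all past allocations but not the order of block sizes, and guesses the arm that is behind (a coin toss when the arms are level).

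**Chance of a correct guess, by position and by number of consented patients ahead in the queue**

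| Position | None waiting | One | Two | Three |
|---|---|---|---|---|
| Block of 2, 1st | 1/2 | 1/2 | 1/2 | 1/2 |
| Block of 2, 2nd | 1 | 1/2 | 1/2 | 1/2 |
| Block of 4, 1st | 1/2 | 1/2 | 1/2 | 1/2 |
| Block of 4, 2nd | 2/3 | 1/2 | 1/2 | 1/2 |
| Block of 4, 3rd | 2/3 | 2/3 | 1/2 | 1/2 |
| Block of 4, 4th | 1 | 2/3 | 2/3 | 1/2 |
| Sum of six | 4.333 | 3.333 | 3.167 | 3 |
| Divided by 6 | 72.2% | 55.6% | 52.8% | 50% |

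The 2/3 entries arise as follows. In a block of 4, the second assignment differs from the first with probability 2/3. The first two agree with probability 1/3, and then the last two are fixed. The third is therefore guessed correctly with probability 1/3 × 1 + 2/3 × 1/2 = 2/3. Simulation of 120-patient lists gave 72.2%, 55.6%, 52.8% and 50.0%.

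**Even-numbered patients, none waiting.** (1 + 2/3 + 1)/3 = 88.9%. For odd-numbered patients: (1/2 + 1/2 + 2/3)/3 = 55.6%.

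**Certain allocations.** A lead of two can arise only halfway through a block of 4, and it fixes both remaining assignments: (1/3 × 2)/6 = 11.1% (simulation 10.8%). If the order of block sizes were also known, the figure would be (1 + 1 + 1/3)/6 = 38.9%.

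**How often someone is waiting.** The trial runs for 13 months. If about 10 of these are for accrual (assumed, keeping 3 for follow-up), 120/10 = 12 patients a month, roughly one every two working days. Often none or one would be waiting.

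**Would larger blocks help?** Expected correct guesses in a block of size 2b, none waiting, are b + 2^(2b−1)/C(2b, b) − 1/2:

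- Size 2: 1.5 (75.0%)
- Size 4: 2.833 (70.8%)
- Size 6: 4.1 (68.3%)
- Size 8: 5.329 (66.6%)

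An equal mix of 4, 6 and 8 gives (2.833 + 4.1 + 5.329)/18 = 68.1%. Block size alone moves the rate only from 72% to 68%. Removing knowledge of past allocations moves it to 50%.

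**The case against.** The strongest reply has four parts.

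1. *The list is properly protected.* An independent statistician makes it, and it is kept in numbered, opaque, sealed envelopes under lock. This stands as far as it goes. A reader might infer that the list is open to the enroller, and the article does not support that: only past assignments become known.

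2. *The 72% does not describe recruitment in general.* A reader might infer that the next arm is largely predictable whenever a patient is approached. It is not. Consent precedes randomization, each patient waiting in between lowers the rate, and even with nobody waiting about 44% of guesses are coin tosses. This part stands: 72% is an upper figure for consent. It applies in full only when nobody is waiting, or at the decision to proceed in theatre.

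3. *The route to bias is assumed.* Nothing in the article gives this researcher control of theatre lists or of the order of operations, the researcher is called independent, and most eligibility criteria are objective. Nor does the article say that the researcher is told the block sizes; their publication does not show that recruiting staff knew them during accrual. This stands against any claim that bias arose. It does not remove the weakness, because nothing says that the sizes are withheld, and independence (not further defined) does not remove foresight.

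4. *Outcome assessors are separate and masked.* This is true and valuable, but it protects against biased assessment, not against selection at entry.

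**Conclusion.** The point holds as a weakness in allocation concealment. One person enrols and opens the envelopes, and with blocks of 2 and 4 in what reads as a single list, past allocations carry information about the next one. The correct-guess rate is up to 72% with nobody waiting (89% for even-numbered patients; about 11% of allocations certain), about 56% with one patient waiting, 53% with two and 50% with three. These figures rest on equal frequency of the two block sizes and on the enroller knowing them, neither of which the article states.

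The article shows an opportunity for selection, not that any took place, and the sample size is unaffected. This is a cheap improvement rather than a flaw that undermines the design.

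**What to change.** Have the envelopes opened at specimen removal by existing staff who take no part in screening, consent, scheduling or the decision to proceed to randomization; the operating-room nurse is one example. Someone with no treating role is also preferable to the anesthesiologist who performs the ESPB. Keep the record of past allocations and the block sizes from the enrolling researcher. With past allocations unknown, the guess rate returns to about 50%. Reword the general concealment statement so that it names who is masked and who is not.

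The cost is a small reassignment of duties among existing staff. Sample size, outcomes and treatment do not change. Regenerating the list with larger blocks is not needed: it would add a change during the trial for a gain of only about four percentage points.

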### Study interventions

The local anesthetic used for regional nerve block in both groups was liposomal bupivacaine (Bupivacaine Liposome Injection; Jiangsu Hengrui Pharmaceuticals Co., Ltd., China). For the ESPB group, a single erector spinae plane block is performed at the T5 vertebral level under ultrasound guidance by an independent anesthesiologist at the end of the surgery. The patient is positioned laterally, and a high-frequency linear ultrasound probe is placed 2–3 cm lateral to the T4 spinous process, then adjusted outward to locate the T5 transverse process in the sagittal plane. The erector spinae muscle is identified above the transverse processes. Under planar ultrasound visualization, the needle is carefully advanced until it contacts the bone of the T5 transverse process. Following the verification of proper needle position through a preliminary injection of 2 mL saline solution, 30 mL of local anesthetic (LB 266 mg mixed with 10 mL normal saline) is slowly administered after confirming the absence of blood or cerebrospinal fluid via aspiration.

For the ICNB group, an experienced surgeon identifies the T3 to T8 intercostal spaces under thoracoscopic visualization at the end of the operation. Subsequently, 3–4 mL of LB is injected into each intercostal space, approximately 3–5 cm lateral to the spinous processes at the T3 to T8 levels. The procedure is considered successful when pleural displacement is observed in all targeted intercostal spaces. In total, 20 mL of LB (266 mg) is administered across the intercostal spaces.

After surgery, all patients are provided with patient-controlled intravenous analgesia (PCIA), consisting of 100 μg sufentanil diluted to 100 mL with normal saline (final concentration: 1 μg/mL). The PCIA device is programmed with the following parameters: a background infusion rate of 1 mL/h, a self-controlled bolus of 2 mL, a lockout interval of 10 min, and a maximum hourly dose of 20 mL. The PCIA is initiated immediately after surgery and continues for 48 h postoperatively. If pain persists, defined as a numeric rating scale (NRS) pain score of ≥4, patients are instructed to self-administer sufentanil via PCIA. If pain remained unrelieved, intravenous rescue opioids (sufentanil, fentanyl, oxycodone, tramadol, or morphine) were permitted. Additionally, both groups will receive an initial intravenous dose of 50 mg flurbiprofen axetil at the end of surgery. This will be followed by two daily doses of 50 mg intravenous flurbiprofen axetil administered at 08:00 and 16:00 (totaling 100 mg per day) as part of the multimodal analgesia regimen on postoperative days 1 and 2.

### Perioperative management

Upon arrival in the operating room, patients receive standard monitoring, including non-invasive blood pressure measurement, electrocardiography, pulse oximetry (SpO_2_), and temperature monitoring. Following anesthesia induction, all patients undergo left or right radial artery catheterization for continuous arterial blood pressure monitoring. The anesthesia induction procedure follows a standardized protocol, involving the sequential administration of propofol (2–2.5 mg/kg), sufentanil (0.3–0.5 μg/kg), and cisatracurium (0.1–0.2 mg/kg). Endotracheal intubation is performed using a double-lumen tube for lung isolation, with proper positioning verified via fiberoptic bronchoscopy. The intraoperative mechanical ventilation protocol followed established lung-protective strategies (18). During one-lung ventilation, tidal volumes were set at 4–6 mL/kg, with an initial PEEP of 5 cmH₂O, followed by individualized adjustment. The inspired oxygen fraction and respiratory rate were modified to maintain SpO₂ ≥ 95% and end-tidal carbon dioxide (EtCO₂) levels between 35 and 45 mmHg during both one-lung and double-lung ventilation. Lung recruitment maneuvers were performed when clinically indicated. Anesthesia is maintained with sevoflurane inhalation, targeting a bispectral index value between 40 and 60. Intraoperative analgesia is provided with sufentanil and remifentanil: sufentanil 0.1–0.2 μg/kg is administered before surgical incision, and remifentanil (0.05–0.2 μg/kg/min) is continuously infused throughout the procedure. Sufentanil (0.1–0.2 μg/kg) is given when the remifentanil infusion is discontinued at the end of the operation. Incremental doses of cisatracurium are given intraoperatively as required.

Intraoperative hypotension (defined as a mean blood pressure [MBP] decrease of >30% from baseline or an MBP of <65 mmHg) would be treated with intravenous ephedrine of 6–10 mg or phenylephrine of 50–100 μg, and bradycardia (defined as heart rate [HR] of <50 beats/min) would be managed with intravenous atropine of 0.3–0.5 mg or ephedrine bolus if coexisting hypotension is present. Hypertension (defined as an MBP increase of >30% of baseline) will be treated with intravenous urapidil 5–10 mg. Tachycardia (defined as HR > 100 beats/min) will be treated with intravenous esmolol 10–20 mg.

At the end of the surgery, all patients receive ondansetron of 8 mg as an antiemetic after the final sutures are placed. Patients are then transferred to the post-anesthesia care unit (PACU) before being moved to the surgical ward. The Modified Aldrete Score is used to assess recovery in PACU, with a score of 9 or higher considered acceptable for discharge. To prevent any impact on pain perception, intravenous sedative drugs will not be administered after surgery.

### Data collection and registration

Trained independent investigators who are blinded to group assignment will collect the patients’ demographic data and follow-up outcomes.

Pain intensity is assessed using the numeric rating scale (NRS, 0–10; 0 = no pain, 10 = worst possible pain) at rest and during activity at 24, 48, and 72 h postoperatively, with a 2-h time window. Quality of Recovery-15 (QoR-15) scores are recorded at the same time points to evaluate overall recovery (19). This questionnaire measures five domains: pain, psychological state, emotional state, independence, and comfort. It consists of 15 statements rated on a 0–10 scale, with total scores ranging from 0 to 150. Higher scores indicate better postoperative recovery. Additionally, the time to the first press on PCIA device and the total amount of opioid consumption through 0–72 h postoperatively are documented. The time to first press on PCIA is measured in hours, calculated as the time of the first press on PCIA minus the time of the end of surgery. Total opioid consumption is standardized by converting all opioids to intravenous morphine milligram equivalents (MMEs) for each patient. For patients discharged before 72 h, follow-up assessments are conducted via telephone. The incidence of chronic pain (defined as NRS score ≥ 1) is evaluated through phone calls at 3 months postoperatively, with a permitted time window of 3 months ±7 days. Furthermore, the time to initiate independent bedside mobilization, and the length of the postoperative hospital stay are recorded. Independent bedside mobilization is defined as the patient being able to perform activities around the bed without assistance from others. The time to initiate independent bedside mobilization is measured in hours, i.e., the time of the event minus the time of the end of surgery.

All data will be entered into electronic case report forms (eCRFs) under the oversight of trained research personnel. An electronic trial database will be generated based on these eCRFs. Once data entry is finalized, the database will be locked and de-identified. The anonymized dataset will subsequently be transferred to an independent statistician for final analysis according to the prespecified statistical plan.

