**Figure 1 fig1:**
[figure not shown]
Study flow diagram. ESPB, erector spinae plane block; ICNB, intercostal nerve block.

**Table 1 tab1:** Schedule of patient enrollment, study interventions, and outcome measurements.

Timepoint	Study period								
	Enrollment	Allocation	Post-allocation						Close-out
	Preoperative visit	specimen removal	End of surgery	PACU	24 h after surgery	48 h after surgery	72 h after surgery	Hospital discharge	90 d after surgery
Enrollment									
Eligibility screening	**╳**								
Written informed consent	**╳**								
Demographic data	**╳**								
Randomization		**╳**							
Allocation		**╳**							
Interventions									
ESPB			**╳**						
ICNB			**╳**						
Measurements									
Pain scores at rest					**╳**	**╳**	**╳**		
Pain scores on activity					**╳**	**╳**	**╳**		
QoR-15 scores					**╳**	**╳**	**╳**		
First press on the PCIA device				**╳**	**╳**	**╳**			
Opioid consumption				**╳**	**╳**	**╳**	**╳**		
Initiate independent bedside mobilization					**╳**	**╳**	**╳**		
Postoperative hospital stay								**╳**	
Adverse events^a^				**╳**	**╳**	**╳**	**╳**		
Incidence of chronic pain									**╳**

According to SPIRIT statement of defining standard protocol items for clinical trials. PACU, post-anesthesia care unit; ESPB, erector spinae plane block; ICNB, intercostal nerve block; QoR-15, Quality of Recovery-15; PCIA, patient-controlled intravenous analgesia.

a Including postoperative nausea and vomiting (PONV), fever, headache, dizziness, itching, constipation, ileus, urinary retention, insomnia, new-onset atrial fibrillation, severe ventricular arrhythmia, cardiac arrest, chest tightness, pulmonary embolism, Pulmonary atelectasis, pneumothorax, chylothorax, Pneumothorax, deep vein thrombosis and organ failure.

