### Study outcomes

The primary outcome of this trial is the average numeric rating scale (NRS) pain scores at rest over 72 h postoperatively (average of three 24-h time points: 24, 48, and 72 h). Secondary outcomes include NRS pain scores at rest and during activity at 24, 48, and 72 h postoperatively; Quality of Recovery 15 scores at 24, 48, and 72 h postoperatively; time to first press on the PCIA device; total amount of opioid consumption within 72 h postoperatively, converted to morphine milliequivalents; the time to initiate independent bedside mobilization, the length of the postoperative hospital stay and incidence of chronic pain (defined as an NRS score ≥ 1) at 3 months post-surgery. Safety outcomes included postoperative adverse events and complications within 72 h, including postoperative nausea and vomiting (PONV), fever, headache, dizziness, itching, constipation, ileus, urinary retention, insomnia, new-onset atrial fibrillation, severe ventricular arrhythmia, cardiac arrest, chest tightness, pulmonary embolism, pulmonary atelectasis, chylothorax, pneumothorax, deep vein thrombosis, and organ failure. The definitions of adverse events are displayed in Supplementary Table S1.

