### Statistical analysis

Descriptive statistics will be used to summarize baseline characteristics and demographic data without conducting between-group comparisons. Continuous data will be reported as median with interquartile ranges (IQR) or means with standard deviations (SD), depending on data distribution. Categorical data will be displayed as counts and percentages. The independent t-test or the Mann–Whitney U test will be used to assess between-group differences in continuous data, while the Chi-squared test or Fisher’s exact test will be applied for categorical data analysis, as appropriate.

For the study outcomes, the treatment effect of study interventions will be evaluated using odds ratios for binary data and differences for continuous data, each reported with 95% confidence intervals. The primary and secondary outcomes will be further analyzed using multivariable linear regression or logistic regression, adjusting for baseline covariates (age, sex, type of surgery, and number of ports). Subgroup analyses for the average pain score will be performed according to age (<60 years old vs. ≥ 60 years old), sex (female vs. male), BMI (< 25 vs. ≥ 25), surgery type (wedge resection vs. segmentectomy vs. lobectomy), and the number of port (single or multiple). Correction for multiple testing is planned for secondary outcomes using the Benjamini-Hochberg method.

The analysis will be performed on the modified intention-to-treat population, comprising all randomized patients who undergo VATS lung resection and for whom primary outcome are available. We do not plan to conduct missing data imputation or interim analysis. A Two-sided *p-*value of <0.05 will be considered statistically significant. Statistical analyses will be performed with R statistical software (version 4.3.0, R Foundation for Statistical Computing) by independent statisticians.

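### No preoperative QoR-15 is scheduled, so the planned adjusted QoR-15 regressions cannot use the patient's own baseline: a small, avoidable loss of precision on a secondary outcome

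*Protocol article*

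**What the plan says.** **When QoR-15 is taken.** Under Data collection and registration, pain is scored "at rest and during activity at 24, 48, and 72 h postoperatively, with a 2-h time window", and QoR-15 "scores are recorded at the same time points to evaluate overall recovery". The scale covers pain, psychological state, emotional state, independence and comfort, "with total scores ranging from 0 to 150". Study outcomes lists as secondary "Quality of Recovery 15 scores at 24, 48, and 72 h postoperatively".

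**What is taken before surgery.** In Table 1 the preoperative visit holds eligibility screening, consent and "Demographic data". The QoR-15 row is marked only in the 24, 48 and 72 h columns.

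**How QoR-15 is analysed.** Under Statistical analysis, "The independent t-test or the Mann–Whitney U test will be used to assess between-group differences in continuous data". Primary and secondary outcomes then go into multivariable regression, "adjusting for baseline covariates (age, sex, type of surgery, and number of ports".

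**When allocation happens.** Under Randomization and blindness: "Randomization will be performed intraoperatively at the time of surgical specimen removal". Anything recorded at the preoperative visit therefore precedes allocation.

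**The concern.** A patient's own earlier score is usually a natural covariate for a later score on the same questionnaire. Several QoR-15 domains, such as emotional state and independence, can differ between patients before any operation. Whatever part of that variation carries over to the postoperative scores stays in the residual variance of the adjusted models, apart from what age, sex, type of surgery and number of ports explain.

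The protocol has already chosen covariate adjustment for this outcome and has a visit at which the score could be taken, so the loss is avoidable. It is also fixed by the schedule: this is a question of data collection, not an analysis detail that an article may leave to a fuller document. What is at stake is the width of three confidence intervals. The sample size was set for pain, and no power is stated for QoR-15.

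**Working it through.** **The plan's own figure.** The Sample size calculation section gives a difference of 1 NRS point, SD 1.75, 80% power, a 0.05 significance level (two-sided under Statistical analysis) and 15% dropout, with 120 patients in total. A two-sample t-test needs 50 per arm. 50 / (1 − 0.15) = 58.8, so 59 per arm or 118 in total, which agrees with 120 after rounding up. This figure concerns pain only. The article gives no precision or power figure for QoR-15.

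**Inputs for QoR-15.**
- Evaluable patients per arm: 60 × (1 − 0.15) = 51.
- Correlation r between preoperative and postoperative QoR-15: not in the documents. It is assumed here, over the range 0.2 to 0.5.

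**Formulas.** Adjusting for a baseline with correlation r multiplies the variance of the treatment difference by 1 − r².
- The confidence interval narrows by 1 − √(1 − r²).
- The equivalent number per arm is 51 / (1 − r²).
- Without a baseline, the difference detectable at 80% power (normal approximation) is (1.960 + 0.842) × √(2/51) = 0.555 SD. With a baseline it is 0.555 × √(1 − r²).

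| r | Variance removed (r²) | CI narrower by | Equivalent n per arm | Detectable difference | Power for 0.555 SD |
|---|---|---|---|---|---|
| none | 0% | 0% | 51.0 | 0.555 SD | 80.0% |
| 0.2 | 4% | 2.0% | 53.1 | 0.544 SD | 81.6% |
| 0.3 | 9% | 4.6% | 56.0 | 0.529 SD | 83.6% |
| 0.4 | 16% | 8.3% | 60.7 | 0.508 SD | 86.4% |
| 0.5 | 25% | 13.4% | 68.0 | 0.480 SD | 89.9% |

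The reference here is an unadjusted comparison with a baseline for every patient. The four planned covariates may already explain part of the same variation, so these gains are best read as upper limits.

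**If only some patients have a baseline.** With a share p measured, the variance removed is roughly p × r². For p = 0.5, chosen as an illustration:
- r = 0.2: 1 − √(1 − 0.02) = 1.0%
- r = 0.3: 1 − √(1 − 0.045) = 2.3%
- r = 0.4: 1 − √(1 − 0.08) = 4.1%
- r = 0.5: 1 − √(1 − 0.125) = 6.5%

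**The case against.** The strongest reply is that nothing here is wrong or contradictory. The text and Table 1 agree, the outcome is the postoperative score and not a change from baseline, and 1:1 randomization makes a comparison of postoperative scores unbiased. All of that stands. What remains is an efficiency gain on one secondary outcome, worth raising only because it costs so little.

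Four further objections also hold in whole or part:

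- **The unadjusted tests gain nothing.** A covariate in the regression does not change a t-test or Mann–Whitney result. The benefit is realised only if the adjusted estimate is the one reported as the main QoR-15 result.
- **The correlation may be low.** The exclusion criteria remove chronic pain, preoperative sedative or analgesic use, uncontrolled psychiatric disorders and neurological disorders. This plausibly narrows the preoperative spread of scores and so weakens r. The range must therefore include values such as 0.2, where the gain is about 2%.
- **Recruitment may be well advanced.** Study design and participants gives a start of 1 December 2024 and anticipated completion on 31 December 2025, so a partial baseline, or none, may be the realistic case.
- **A missing-baseline indicator needs a filled-in constant.** That sits awkwardly with the protocol's statement that missing data will not be imputed.

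A reader might also infer more than the documents support:

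- *That the QoR-15 comparison is biased, or that a chance imbalance invalidates it.* Randomization balances the preoperative score in expectation, and the confidence interval already allows for chance imbalance.
- *That the trial has nothing at baseline to adjust for.* Four covariates are planned; only the QoR-15 baseline is absent.
- *That the gain is worth 10% to 33% more patients.* Those figures are 1 / (1 − r²) − 1 at r = 0.3 and 0.5. They need an undocumented correlation, no overlap with the planned covariates and a baseline score for every patient.

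**Conclusion.** The point holds as a minor improvement. The absence of a preoperative QoR-15 is explicit in Table 1, and it prevents the three planned QoR-15 regressions from using the patient's own starting score. The cost is precision on a secondary outcome; validity, the primary outcome and the sample size are untouched.

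The size rests on an assumed correlation. For r between 0.2 and 0.5 the confidence interval would narrow by at most about 2% to 13%, less on top of the planned covariates and roughly in proportion to the share of patients measured before surgery. At r of 0.3 or below the benefit is small even with complete baselines.

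**What to change.** 1. In Table 1, mark QoR-15 at the preoperative visit, after consent. Randomization comes later, so the score cannot be influenced by allocation.
2. Enter that score as a covariate, alongside the four already planned, in the linear regressions of QoR-15 at 24, 48 and 72 h.
3. State that the adjusted difference with its 95% confidence interval is the main QoR-15 result at each time, and that its p-value enters the Benjamini-Hochberg procedure.
4. If recruitment is under way, start with the next patient. For those enrolled earlier, set the missing baseline to a constant, add a missing-baseline indicator to the model, and record this as an exception to the no-imputation statement. The exception covers a baseline covariate only; no outcome is filled in.
5. If recruitment is complete, keep the present models and list the missing QoR-15 baseline among the limitations, where it does not now appear.

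The cost is a few minutes per patient for a 15-item form at a visit that already takes place, and one extra covariate (plus an indicator if step 4 applies).
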